#### 5.5.2 Secondary endpoints:

- 24 hours post-1st dose, and 36 hours post-12th dose cervico-vaginal lavage MAb levels
- 24 hours post-1st dose, and 36 hours post-12th dose Mab levels in self-sampled vaginal aspirate
- 8 hours post-1st dose, and 12 hours post-12th dose serum MAb levels
- Number of grade 3 or above genital adverse events (see Appendix 6) during the dosing or follow up period
- Number of grade 3 or above other clinical or laboratory adverse (see Appendix 7) events confirmed at examination or on repeat testing respectively during the dosing or follow up period
- Number of events attributable to the study gel leading to discontinuation of gel

Data on local events listed above will be solicited with specific questions and/or cervico-vaginal and colposcopic examination. Data on laboratory events will be collected through the routine tests or in response to a clinical event. Data on other events will be collected with open questions. Detail on the analysis of MAbs in vaginal secretions and serum samples can be found in section 10.4.

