### **6.3 Number and source of participants**

We will aim to recruit and randomise 30 healthy HIV negative female volunteers. All 30 participants will be randomised to one of the three trial arms, subject to complete fulfilment of the eligibility criteria.

Participants will be recruited by advertising in the York area, including via the GU medicine clinic, the University of York, York St John University, mailing lists, and by coverage and advertising in local media.

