### **9.4.2 Discontinuation of dosing**

Discontinuation of dosing describes a permanent cessation of study gel use. Discontinuation of dosing will occur in the presence of:

- a grade 3 or above solicited genital adverse event
- a grade 3 or above clinical or laboratory event
- any clinical event at the discretion of the CI which should lead to discontinuation of study gel

Interruption or discontinuation of gel use may also occur if the participant desires to stop study gel use. Wherever possible, participants who discontinue study gel use either by choice or following advice will continue to adhere to the follow up schedule up to the final visit.

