## **9.5 Temporarily halting or stopping the study**

In the case of 3 women experiencing either a grade 3 or above genital adverse event or grade 3 or above clinical or laboratory adverse event, the study will be temporarily halted pending unblinded review by the Data Monitoring Committee (DMC). Several severe or

serious AEs, which are probable in relation to the study gel, will lead to the study being terminated at that point. The decision to stop the study rests on the CI, with recommendations from the DMC (see section 11.6.3).

The Sponsor reserves the right to terminate the study at any time.

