#### 10.2.2 Statistical analyses of primary and secondary endpoints

Antibody levels in vaginal Weck-Cel samples, cervico-vaginal lavage and serum samples will be summarised for each treatment group as minimum, median, and maximum at each time-point. Treatment groups will be compared using the Kruskal Wallis test corrected for ties. Where the Kruskal Wallis test is statistically significant,  $P < 0.05$ , the two active treatment groups will be compared using a Mann Whitney U test, to check whether there is evidence that the higher dose produces higher antibody concentrations.

Half-life will be estimated for each antibody using only the groups which received an active dose, and observations at 1, 8, and 24 hours after the first dose. The method will be to assume an exponential decay curve. If we cannot assume this, a half-life is not a meaningful estimate. A log transformation of the observed concentration will be used and an analysis of covariance model fitted with time as continuous predictor and participant as a categorical factor. Two checks on the assumptions will be made. Linearity will be checked by including and testing a time squared term. Uniformity of the half life will be checked by testing an interaction between time and participant. If the assumptions are met, half-life will be estimated by  $\log(2)/\text{slope}$ . The 95% confidence interval will be found from the usual confidence interval for the slope. If assumptions are not met, analysis will then be data-driven.

All analyses of antibody levels will be carried out using the raw data and Weck-Cel antibody concentrations will also be analysed using data adjusted for the dilution factor. All "not detectable" observations will remain "not detectable" and will not be adjusted. The dilution factor will be calculated as

$(\text{volume of processing buffer} + \text{Weck-Cel sample volume}) / \text{Weck-Cel sample volume}$

Adjustment for the dilution factor will be to multiply the observed antibody concentration by this dilution factor. Volume of processing buffer will be 600 microlitres.

Analysis of the safety endpoints will involve comparing counts of adverse event rates in the three groups using negative binomial regression.

Comparisons will be made for the following:

- Number of grade 3 or above solicited genital adverse events or events attributable to the study gel leading to discontinuation of gel (Appendix 6) during the dosing or follow up period

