## **10.3 Randomisation scheme and maintenance of blinding**

### **10.3.1 Randomisation code**

Randomisation will be carried out by the York Trials Unit, University of York. Subject numbers 01 to 30 will be randomised to Mabgel (high dose), Mabgel (low dose) or placebo using blocked randomisation of mixed block sizes. Randomisation will be in the ratio of 1:1:1. The randomisation program will be generated using Microsoft Visual Basic and a copy of the generated data stored in Microsoft SQL Server. The randomisation list will be posted to Polymun Scientific, Austria for the purposes of labelling the study gel. Personnel carrying out subsequent analyses will not have access to this list.

Participants will only be allocated a randomised subject number when they have provided informed consent to take part in the trial, and all screening tests have been carried out to ensure they meet the eligibility criteria. Subject numbers will then be allocated on a sequential basis at visit 2 after cervico-vaginal examination.

In order to maintain double-blinding, neither the CI nor the Investigators will have direct access to the randomisation codes.

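### With 10 women per arm and severe events expected to be rare, the negative binomial regression named for the grade 3+ safety counts will usually give no usable estimate, and two of the listed endpoints are merged

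*Protocol*

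**What the plan says.** Protocol section 10.2.2 fixes the safety model: "Analysis of the safety endpoints will involve comparing counts of adverse event rates in the three groups using negative binomial regression". It lists four comparisons under it. The first is "Number of grade 3 or above solicited genital adverse events or events attributable to the study gel leading to discontinuation of gel". The second is the number of other grade 3+ clinical or laboratory events. The third and fourth are all adverse events, and those classed as possibly or probably treatment-related. No alternative is given for sparse data, although the same section says what happens if the half-life model's assumptions fail.

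Section 5.5.2 lists three safety endpoints. One of them stands alone as "Number of events attributable to the study gel leading to discontinuation of gel".

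On size, section 6.3 says "We will aim to recruit and randomise 30 healthy HIV negative female volunteers" and section 10.3.1 says "Randomisation will be in the ratio of 1:1:1". On frequency, section 8.5 does not expect adverse events to interrupt or end dosing, and section 13.4 regards antibody-related reactions as very improbable. Neither gives a rate.

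Under section 9.4.2 a woman stops gel permanently after "a grade 3 or above solicited genital adverse event" or a grade 3+ clinical or laboratory event, but where possible stays in follow-up to the final visit. Section 9.5 begins "In the case of 3 women experiencing either a grade 3 or above genital adverse event" and adds grade 3+ clinical or laboratory events. The consequence is a temporary halt for unblinded review by the Data Monitoring Committee.

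**The concern.** A three-arm negative binomial regression needs at least one event in every arm to give finite rate ratios. It also needs some women with repeat events to estimate a dispersion above zero. Ten women per arm, with severe events expected to be rare, will often supply neither. The placebo arm is there partly to strengthen the safety comparison (section 5.4), and section 9.3.2 requires statistical analysis of all adverse events. If the named model gives nothing usable, the replacement is chosen after the data are seen.

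The endpoint definition is a second, independent problem. The first comparison adds "or events attributable to the study gel leading to discontinuation of gel" to the grade 3+ genital events. Section 9.4.2 requires discontinuation for any grade 3+ clinical or laboratory event. If such an event is attributable to the gel and leads to discontinuation, it counts in the first comparison as a discontinuation and in the second as a grade 3+ event. This follows from the text and needs no assumption about rates.

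**Working it through.** The protocol states no power or event-rate figure for safety, so there is no figure of its own to reproduce.

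**Inputs.** 30 women (6.3), 1:1:1 (10.3.1), hence 30/3 = 10 per arm. Assumed, because not stated: no dropout, equal risk in the three arms, and a per-woman risk of 1% to 20%.

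**Step 1: empty arm, given k affected women among 30.** For k ≥ 1, P = [3·C(20,k) − 3·C(10,k)] / C(30,k).

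| k | Calculation | P(at least one empty arm) |
|---|---|---|
| 1 | (60 − 30)/30 | 100% |
| 2 | (570 − 135)/435 | 100% |
| 3 | (3420 − 360)/4060 | 75.4% |
| 4 | (14535 − 630)/27405 | 50.7% |
| 5 | (46512 − 756)/142506 | 32.1% |
| 6 | (116280 − 630)/593775 | 19.5% |

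**Step 2: empty arm by assumed per-woman risk p.** P = 1 − [1 − (1 − p)^10]^3. The last column is the binomial chance that at least 3 of 30 women are affected.

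| p | (1 − p)^10 | P(empty arm) | P(≥3 women affected) |
|---|---|---|---|
| 1% | 0.904 | 99.9% | 0.3% |
| 5% | 0.599 | 93.5% | 18.8% |
| 10% | 0.349 | 72.4% | 58.9% |
| 20% | 0.107 | 28.9% | 95.6% |

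**Step 3: what the fit returns** (maximum likelihood).
- Events 2/1/0: coefficient for the empty arm −25.2, no standard error. A Poisson fit gives a standard error of about 11,459.
- Events 0/0/0: singular matrix.
- Events 1/1/1, one per woman: dispersion at zero, no negative binomial standard errors. The Poisson standard error of the log rate ratio is √(1/1 + 1/1) = 1.41, so the 95% interval runs from 1/16 to 16 (exp(1.96 × 1.41) ≈ 16).
- One woman with two events in one arm and one woman with one event in each other arm: converges, with dispersion 3.6 (SE 5.6) and log rate ratio SE 1.49.

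In 300 simulated trials per scenario, with and without overdispersion, an empty arm or zero dispersion occurred in about 99–100% at a mean of 0.05 events per woman, 94% at 0.1, and 70–86% at 0.2.

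**Step 4: the all-event count.** At an assumed 2–3 overdispersed events per woman, at most 1% of simulated trials had either problem. Without overdispersion no arm was empty, but dispersion was at zero in about 70%. Poisson is then the appropriate model.

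**Step 5: what exact limits give.** The Clopper-Pearson two-sided 95% upper limit for zero events in n women is 1 − 0.025^(1/n). For 0/10 this is 30.8%; for 0/20 it is 16.8%.

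**The case against.** Two stronger readings are tempting, and the protocol supports neither. A reader might infer that the stopping rules cap grade 3+ events at about three. Section 9.5 prescribes a temporary halt at three affected women, after which the study may resume. Section 9.4.2 stops gel, not observation, so a second event in the same woman still counts. Gel-attributable discontinuations below grade 3 do not feed the halt at all. The rules make repeat and numerous events less likely; the main reason for sparse data is 10 per arm with events expected to be rare. A reader might also infer that the model cannot be fitted at all. Step 3 shows otherwise: some sparse patterns converge, and others reduce to Poisson with a finite but very wide interval.

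The empty-arm probability also falls quickly, to 20% with six affected women and 29% at a 20% risk, and every rate used is an assumption. That stands, so the range is shown.

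Section 10.2 defers detail to a statistical analysis plan that is not at hand, and 10.2.2 does not exclude tabulations or exact limits. A fallback may exist there, and its absence from the protocol alone would be no finding. The point is narrower: the protocol itself names this model for these endpoints.

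Finally, exact tests add computability, not power. If all three affected women were on active gel (3/20 versus 0/10), Fisher's two-sided p = (1140 + 900 + 120)/4060 = 0.53. This stands, so the exact limits should carry the message. Counting women also departs from the event-count wording of 5.5.2, so event counts need to be kept alongside.

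**Conclusion.** The point holds for the two grade 3+ comparisons: followed as written, the named regression will usually give no usable estimate. That certain patterns defeat it is a matter of arithmetic. How often they occur depends on the unstated event rate, with the failure close to certain at 1–5% risk per woman and a minority outcome for empty arms at 20%, where zero dispersion remains common. It does not extend to the all-event count at the rates assumed.

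The mismatch between 10.2.2 and 5.5.2, and the resulting double entry of some events, holds regardless of rates. It does not show that the two merged endpoints are largely the same events: 9.4.2 also allows discretionary discontinuation, and the endpoint requires attribution to the gel.

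Severity: should-fix. Safety is the secondary objective, the protocol makes no power claim, and the halting rule counts women and does not use the model's output.

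**What to change.** Reword section 10.2.2 as follows.

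- Analyse the three safety endpoints of 5.5.2 separately: grade 3+ genital events, other grade 3+ clinical or laboratory events, and gel-attributable events leading to discontinuation.
- For each, tabulate event counts and report the number of women with at least one event, per arm and for pooled active, with Clopper-Pearson 95% confidence intervals.
- If a test is wanted, use the Fisher-Freeman-Halton exact test across the three groups, with pooled active versus placebo as supportive, and state that power is minimal.
- Keep negative binomial regression for the all-event count and the possibly or probably related count. State the fallback: the same exact summaries if an arm has no events, and Poisson if the dispersion estimate is zero.

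The cost is a change of analysis wording; no data collection changes. The downside is that repeat events in the same woman appear only in the event counts and listings.

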- Number of grade 3 or above other clinical or laboratory adverse (Appendix 7) events confirmed at examination or on repeat testing respectively during the dosing or follow up period
- All adverse events (irrespective of assigned relationship to study gel)
- All adverse events classed as possibly or probably treatment-related.

Details of sub-study analyses are provided in section 12.

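### Section 10.2.2 joins grade 3+ genital events and gel-attributable discontinuations, separate endpoints in section 5.5.2, into one count, so neither is compared on its own as defined

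*Protocol*

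**What the plan says.** Protocol section 5.5.2 sets out the safety endpoints as separate items. One is "Number of grade 3 or above genital adverse events (see Appendix 6) during the dosing or follow up period". Another is "Number of events attributable to the study gel leading to discontinuation of gel", which carries no restriction by body site, grade or appendix. Between them stands the count of grade 3+ other clinical or laboratory events, tied to Appendix 7. The study summary (section 1) gives the same three items.

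Section 10.2.2 then lists the safety counts to be compared across the three arms by negative binomial regression:

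- "Number of grade 3 or above solicited genital adverse events or events attributable to the study gel leading to discontinuation of gel (Appendix 6"; the line continues with the dosing or follow-up period
- "Number of grade 3 or above other clinical or laboratory adverse (Appendix 7) events confirmed at examination or on repeat testing respectively"
- "All adverse events (irrespective of assigned relationship to study gel"
- "All adverse events classed as possibly or probably treatment-related"

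Section 9.4.2 gives the grounds for permanent discontinuation. They include "a grade 3 or above solicited genital adverse event", but also "a grade 3 or above clinical or laboratory event" and, at the chief investigator's discretion, any clinical event.

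**The concern.** The first comparison joins with the word *or* two things that the endpoint section keeps apart. One is a severity count on a genital scale. The other is a count of events that the investigator attributed to the gel and that ended dosing, whatever their site or grade. A combined count answers neither question. A difference between arms could come from local reactions, from systemic events or from mild events that stopped dosing, and the comparison would not show which.

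This is the first intravaginal use of these antibodies in humans, and section 5.4 gives the validity of the safety endpoint analyses as one reason for the placebo arm. Severe local reactions and gel-attributable discontinuations are two results that a reader of the report will look for separately.

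**Working it through.** No sample size, power or error rate is involved, so the check sets the sections side by side.

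**Step 1: endpoints against comparisons.** Call the section 5.5.2 endpoints A (grade 3+ genital, Appendix 6), B (gel-attributable events leading to discontinuation) and C (grade 3+ other clinical or laboratory, Appendix 7). The section 10.2.2 list is: A or B; C; all adverse events; possibly or probably related adverse events. Endpoints defined: 3. Compared on their own as defined: 1 (C). A and B appear only in the merged line.

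**Step 2: can B contain anything that A does not?** Section 9.4.2 makes a grade 3+ solicited genital event a ground for discontinuation, so A and B overlap where such an event is judged attributable. Section 9.4.2 also admits grade 3+ clinical or laboratory events and discretionary stops for any clinical event. B can therefore contain non-genital events and events below grade 3.

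**Step 3: what the merged line counts under each reading of the tag.** The reference to Appendix 6 closes the joined phrase. In the broad reading it describes only the genital part; in the narrow reading it limits the whole line to genital events.

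| Event | Endpoint(s) in 5.5.2 | Merged line, broad | Merged line, narrow |
|---|---|---|---|
| Genital, grade 3+, attributable, gel stopped | A and B | counted | counted |
| Genital, grade 3+, not attributable | A only | counted | counted |
| Genital, below grade 3, attributable, gel stopped | B only | counted | counted |
| Non-genital, grade 3+, confirmed, attributable, gel stopped | B and C | counted | not counted |
| Non-genital, below grade 3, attributable, gel stopped | B only | counted | not counted |

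Under either reading the merged count equals neither A nor B. Row 2 is in the count but not in B, and row 3 is in the count but not in A. Under the broad reading, rows 4 and 5 also enter without being genital. Under the narrow reading, rows 4 and 5 are missing from any discontinuation comparison.

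**Step 4: size.** Section 6.3 plans 30 women and section 10.3.1 randomises 1:1:1, so 30 / 3 = 10 per arm. Under the broad reading, one attributable non-genital event that stops dosing moves an arm's merged count from 0 to 1, or from 0% to 1/10 = 10% of its women, with no genital event at all.

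**The case against.** The strongest reply has four parts.

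*The tag may already limit the line to genital events.* The first item ends with Appendix 6 and the second carries Appendix 7, so a parallel reading would send systemic events to the second item. This stands to the extent that a reader should not infer that systemic events certainly enter the merged count; they can. The narrow reading is the weaker one, because section 5.5.2 attaches Appendix 6 to the genital endpoint alone and that appendix grades genital reactions without defining any discontinuation event. Even if it is right, B is still not analysed as defined.

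*Discontinuations are not wholly absent.* They enter the merged count, and the underlying events enter the related-event comparison if classed as possibly or probably related. A reader might infer that the endpoint is never compared at all; the documents support only that it is never compared on its own. The related-event comparison does not pick out events that stopped dosing.

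*Overlap between counts is not caused by the merge.* A reader might object that one systemic event could be counted twice. Under section 5.5.2 as written, a confirmed, attributable grade 3+ laboratory event that stops gel already belongs to both B and C, and it would still do so after a split. Double counting is therefore not part of this point.

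*The practical effect is small.* Section 8.5 does not expect discontinuation for adverse events, section 13.4 calls antibody-related reactions extremely unlikely, and with about 10 women per arm a regression on counts of 0 or 1 says little, merged or split. The halting rule in section 9.5 uses its own criteria. All of this stands, and it limits the point to the interpretation and reporting of secondary safety results.

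A reader might also infer that the word *solicited* in section 10.2.2 narrows the genital endpoint. It does not: section 9.1 defines solicited genital events by the Appendix 6 list, and section 5.5.2 refers to the same appendix.

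**Conclusion.** The inconsistency is real and visible in the protocol itself. Followed as written, section 10.2.2 compares neither grade 3+ genital events nor gel-attributable discontinuations on their own as section 5.5.2 defines them. The merged count can take in non-genital or below-grade-3 events or, on the narrower reading of the tag, leaves non-genital discontinuations out of any discontinuation comparison.

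The consequence is confined to the clarity of the secondary safety results. The primary pharmacokinetic endpoint is untouched and no stopping criterion depends on the line. How often it would matter cannot be calculated, because the protocol gives no expected event rates; the shift from 0 to 1 in an arm of 10 illustrates a single event and is not a forecast. The statistical analysis plan to which section 10.2 refers was not available. It may separate the counts, but the protocol's own list would still disagree with its endpoint section.

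**What to change.** Replace the first line of the section 10.2.2 list with two items that match section 5.5.2:

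- (a) grade 3+ genital adverse events, with the Appendix 6 reference attached to this item only;
- (b) gel-attributable events leading to discontinuation, each listed as genital or non-genital.

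Add one sentence saying that (b) may overlap (a) and the other clinical or laboratory count, and is not added to them. Carry the same wording into the statistical analysis plan.

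The cost is a wording change and one extra table row. The adverse event grade, attribution and discontinuation data are already to be collected, so no visits, samples or participants are added. The drawback is that each separate count is likely to be smaller than the merged one, so the regression on each will be less informative. At this sample size a plain listing of the events by arm will carry most of the information.

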| Adverse Reaction (AR):                | 
Any untoward and unintended response in a subject to an IMP related to any dose administered to that subject.
 
All AEs judged by either the reporting investigator or the Sponsor for which there is at least some evidence or argument to support a causal relationship to a medicinal product qualify as adverse reactions.
 
Note: All adverse reactions are adverse events
                                                                                                                                                                                                                                                                                                                                                                                                                                                                                                                                         |
| Unexpected Adverse Reaction:          | An AR, the nature or severity of which is not consistent with the applicable product information in the investigator's brochure.                                                                                                                                                                                                                                                                                                                                                                                                                                                                                                                                                                                                                                                                                                                                                                                                                       |

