## 9.2 Causality

The assignment of the causality should be made by the CI, or Clinical Investigator as delegated by the CI, using the definitions in the table below. The Investigator will use clinical judgement to determine the relationship. Alternative causes, such as underlying illness, concomitant therapy, other risk factors etc. will be considered. The Investigator should also consult the Investigator Brochure.

| Relationship     | Description                                                                                                                                                                                                                 | Event type |
|-------------------------|------------------------------------------------------------------------------------------------------------------------------------------------------------------------------------------------------------------------------------|-------------------|
| Not related      | There is no evidence of any causal relationship. The temporal relationship of the onset of the event, relative to administration of the IMP, is not reasonable or another cause can by itself explain the occurrence of the event. | AE/SAE            |
| Unlikely         | The temporal relationship of the onset of the event, relative to administration of the IMP, is reasonable but is more likely to have another cause which can by itself explain the occurrence of the event.                        | AE/SAE            |
| Possibly Related | The temporal relationship of the onset of the event, relative to administration of the IMP, is reasonable but the event could have been due to another, equally likely cause.                                                      | AR/SAR/
SUSAR  |
| Probably Related | The temporal relationship of the onset of the event, relative to administration of the IMP, is reasonable and the event is more likely explained by the product than any other cause                                               | AR/SAR/
SUSAR  |

|                           |                                                                                                                                                             |              |
|---------------------------|-------------------------------------------------------------------------------------------------------------------------------------------------------------|--------------|

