| Definitely Related | The temporal relationship of the onset of the event, relative to administration of the IMP, is reasonable and there is no other cause to explain the event. | AR/SAR/SUSAR |
| Not assessable     | There is insufficient or incomplete evidence to make a clinical judgement of the causal relationship.                                                       |              |

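### The treatment-related adverse event comparison in section 10.2.2 names two of the three causality categories that section 9.2 counts as adverse reactions, and omits Definitely Related

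*Protocol*

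**What the plan says.** Protocol section 9.2 has the investigator assign causality "using the definitions in the table below". That table has six categories: Not related, Unlikely, Possibly Related, Probably Related, Definitely Related and Not assessable. Three carry the event type AR/SAR/SUSAR:

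- Possibly Related: timing is reasonable but "the event could have been due to another, equally likely cause".
- Probably Related: timing is reasonable and "the event is more likely explained by the product than any other cause".
- Definitely Related: the timing "is reasonable and there is no other cause to explain the event".

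Not assessable has no event type. Section 9.1 defines an adverse reaction broadly: all events with "at least some evidence or argument to support a causal relationship to a medicinal product qualify as adverse reactions".

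Section 10.2.2 lists four safety comparisons by negative binomial regression:

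1. Grade 3 or above solicited genital events, or attributable events leading to discontinuation of gel.
2. Grade 3 or above other clinical or laboratory events.
3. All adverse events, whatever their causality.
4. "All adverse events classed as possibly or probably treatment-related".

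Section 9.5, on termination, also uses a single causality word: "serious AEs, which are probable in relation to the study gel, will lead to the study being terminated at that point".

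**The concern.** The fourth comparison is the only one that covers events of every grade and selects them by causality. It is meant to isolate what the gel caused, yet its wording stops one step short of the top of the protocol's own scale. An event with no explanation other than the gel is not classed as possibly related and not classed as probably related, so a programmer following the text would not select it.

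Safety is the secondary objective (section 4), and section 5.4 gives the validity of the safety analyses as one reason for having a placebo arm. With 30 participants randomised 1:1:1, about 10 per arm, a few misplaced events could visibly change this count. The protocol does not leave the set of related events open for the statistical analysis plan. It states a set, and that set disagrees with section 9.2.

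**Working it through.** The plan gives no figure to reproduce. The check matches each category in the section 9.2 table with the fourth comparison in section 10.2.2.

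| Category (9.2) | Event type (9.2) | Named in the related-event comparison (10.2.2) |
|---|---|---|
| Not related | AE/SAE | No |
| Unlikely | AE/SAE | No |
| Possibly Related | AR/SAR/SUSAR | Yes |
| Probably Related | AR/SAR/SUSAR | Yes |
| Definitely Related | AR/SAR/SUSAR | **No** |
| Not assessable | blank | No |

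Three of six categories are adverse reactions, and the comparison names two of those three.

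**Could probable be read to include definite?** The definitions separate them. Probable weighs the product against other causes and finds it the likelier. Definite requires that no other cause exists. Section 10.2.2 speaks of how events are classed, which points to the category recorded. It does not say at least possibly related, and it does not refer to adverse reactions as a group.

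**Size within an arm.** Let *R* be the number of events classed possible or probable, and *D* the number classed definite.

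- Count as written: *R*
- Count of adverse reactions under 9.1 and 9.2: *R* + *D*
- Shortfall: *D*, which is zero or more
- Share missed: *D* / (*R* + *D*)

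The count can only be understated. The protocol gives no adverse event rates, so no value can be put on *D*.

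**Effect between arms.** Take an active arm (subscript 1) and placebo (subscript 0), with equal exposure and non-zero *R* in both. The ratio as written is *R*₁/*R*₀. The full ratio is (*R*₁ + *D*₁)/(*R*₀ + *D*₀). The full ratio is the larger one only when *D*₁/*R*₁ > *D*₀/*R*₀, and the smaller one when that inequality is reversed. The protocol does not show which case applies.

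**Where a definite event is still counted.**

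- Any grade: in the comparison of all adverse events, mixed with unrelated events.
- Grade 3 or above: in comparison 1 if it is a solicited genital event, or in comparison 2 if it is another event confirmed as that item requires.
- Leading to permanent discontinuation and attributable to the gel: in comparison 1, whatever its causality category.
- Grade 1 or 2 without discontinuation: in no comparison based on attribution.

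The last case is realistic. Section 13.4 anticipates minor local effects, usually mild. Section 9.4.1 treats a grade 2 solicited genital event as a reason for interruption, which is distinct from discontinuation in section 9.4.2.

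**The case against.** The strongest reply is that little is lost. Three of the four comparisons are untouched, and the one directly above the affected item counts every event whatever its cause. Section 9.3.2 also requires all adverse events and reactions to be analysed and reported. The related-event count is not among the safety endpoints in section 5.5.2, the primary objective is pharmacokinetic, and section 13.4 regards antibody-related reactions as extremely unlikely. This is probably a drafting slip. All of that stands and limits the weight of the point. It does not make the wording right.

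A reader might infer more: that dropping definite events makes the active gels look safer than placebo. The documents do not support this. Section 13.4 expects events to come from the dosing procedure and the vehicle, and by section 8.1 the placebo has the same composition without the antibodies. Causality is assigned by staff without direct access to the codes (sections 9.2 and 10.3.1). Section 13.4 also names competing causes, such as examination, sampling and the applicator, which make a definite classification hard to reach in any arm.

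A reader might also infer from section 9.5 that definite events could not stop the trial. That does not follow either. The halt after three women with grade 3 or above events ignores causality and leads to unblinded review by the data monitoring committee. The decision to stop rests with the Chief Investigator on that committee's recommendations, and the sponsor may terminate at any time.

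Finally, the unseen statistical analysis plan might define related events correctly. It would then differ from the protocol, which would still need correcting.

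**Conclusion.** The inconsistency is real, and the rule is wrong as written. Every Definitely Related event falls outside the treatment-related comparison, although sections 9.1 and 9.2 make it an adverse reaction. The shortfall in each arm equals the number of definite events. That number is unknown and may be small or zero. One of four listed safety comparisons is affected, and it is not a listed endpoint. No direction of bias between arms can be claimed, and the events are not lost from the trial's safety reporting.

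This rests on reading the comparison as referring to the categories recorded under section 9.2, which is its plain sense. In section 9.5 the matter is one of wording only: probable should be reconciled with the section 9.2 categories. The handling of Not assessable events ("There is insufficient or incomplete evidence to make a clinical judgement of the causal relationship") can be left to the statistical analysis plan and is not part of this finding.

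**What to change.** Reword the fourth comparison in section 10.2.2 to cover adverse events classed as possibly, probably or definitely treatment-related, that is, all categories mapped to AR/SAR/SUSAR in section 9.2. It then covers three of three adverse reaction categories and agrees with section 9.1. Check that the statistical analysis plan and the analysis program use the same set.

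Reconcile the causality word in the termination sentence of section 9.5 with the section 9.2 table, so that it is clear which categories are meant. No particular stopping rule is proposed here.

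The cost is one phrase in section 10.2.2, a clarification in section 9.5, and one selection condition in the program. Causality is already recorded on the full scale, so no new data or participants are needed. The change should be made before the data are analysed.
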